#### Qualitative study

The qualitative study will include focus group interviews and individual interviews focusing on study participants’ perceptions of these technological tools (e.g., Are Glasklart or iBAC easy to use? Are they perceived as good support/help in the treatment?).

#### Instruments

Demographics: age, gender, occupation, and marital status (baseline only).Timeline follow back: structured interview for assessment of alcohol consumption during the last 30 days [27].Alcohol Use Disorder Identification Test (AUDIT) questionnaire [28], modified to the 3-month reference period in the follow-up.Severity of alcohol dependence is measured by the number of fulfilled diagnostic criteria for the diagnosis alcohol dependence, according to ICD-10.Short Alcohol Dependence Data (SADD) [29, 30]: this instrument is currently undergoing Swedish validation and will be published during 2018.Client Satisfaction Questionnaire (CSQ) [31].The Hospital Anxiety Depression Scale (HAD) [32]: 14 items scored 0–3 based on how the respondent felt during the past week.The Short Form Health Survey (SF-12) [33]: 12 items assess functional health and wellbeing from the respondent’s perspective.Phosphatidylethanol (PEth): blood samples will be collected by staff at Karolinska Universitetssjukhusets Laboratorium (KS Lab) in Stockholm and will be analyzed at KemLab/LS Laboratorium. The results will be delivered through the electronic patient record system (Take Care) within 2–3 days. The results will be printed and anonymized by the study coordinator and then placed in the CRF.

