### Baseline and follow-up assessments

Baseline data for this study, the TLFB interview, the AUDIT questionnaire, and the biomarker PEth, as well as diagnostic instruments for the diagnosis of alcohol dependence are collected routinely at intake for all patients at Riddargatan 1.

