#### RCT outcome measures

##### Primary outcome measure

The primary outcome is the number of days with heavy drinking, defined as four or more standard drinks (12 g alcohol/drink), measured by the timeline follow back instrument (TLFB) and AUDIT.

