##### Secondary outcome measures

The secondary outcomes are weekly alcohol consumption, measured by TLFB and AUDIT, and PEth values in blood at 3-month and 6-month follow-up, and the number of days with BAC levels exceeding 60 mg/100 ml.

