### Statistical analyses and power calculation

The sample size has been estimated from the primary outcome variable, heavy drinking days during the past 30 days before baseline, at 3 months and at 6 months after baseline. Based on the assumption that the effect size of the intervention will be in the range of 0.4 SD in groupwise comparisons (alpha 5% and two-tailed tests) we need at least 98 individuals in each of the three treatment arms, and given an expected 25% dropout rate this motivates our choice of *N* = 375.

Data will be analyzed according to intention to treat (ITT). A secondary analysis will be per protocol for those participants who have contributed data at baseline and at 3-month follow-up. Primary and secondary outcome measures will be analyzed through ANOVA for repeated measures, with time (baseline, 3 months, and 6 months) as the dependent variable and type of intervention (TAU, or TAU + Glasklart, or TAU+ iBAC) as the independent variable.

A multiple regression analysis will be performed to investigate the extent to which the different predictor variables (consumption level and pattern, severity of dependence) contribute to the variation in the primary and secondary outcome measures.

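### AUDIT changes its reference period after baseline yet enters one repeated-measures ANOVA, so AUDIT change over time is partly an artefact of the window

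*Protocol article*

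**What the plan says.** All statements are in the protocol article.

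- **Role of AUDIT.** Under Primary outcome measure, heavy drinking days are "measured by the timeline follow back instrument (TLFB) and AUDIT". Under Secondary outcome measures: "The secondary outcomes are weekly alcohol consumption, measured by TLFB and AUDIT".
- **Baseline form.** Baseline and follow-up assessments lists AUDIT among the data that "are collected routinely at intake for all patients at Riddargatan 1". No reference period is given for this form.
- **Follow-up form.** Instruments says that AUDIT is "modified to the 3-month reference period in the follow-up".
- **TLFB, for contrast.** Instruments describes it as a "structured interview for assessment of alcohol consumption during the last 30 days", with no change between visits.
- **Analysis.** Statistical analyses and power calculation says: "Primary and secondary outcome measures will be analyzed through ANOVA for repeated measures", "with time (baseline, 3 months, and 6 months) as the dependent variable". I read time as the within-subject factor, with arm as the between-subject factor.

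No separate handling of the changed AUDIT window is described.

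**The concern.** A repeated-measures ANOVA assumes that the same quantity is observed at each level of time. For AUDIT, the first level comes from the routine intake questionnaire and the other two from a version reworded to cover 3 months. A form that is modified at follow-up is not the form used before, so the window changes exactly where baseline meets follow-up.

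Two things are at stake. First, a fall in AUDIT from baseline, within an arm or as a main effect of time, could be read as improvement when part of it reflects the period asked about. Second, the arm-by-time test uses the baseline as a level on the same footing as the follow-ups. If the intake form has a different variance or correlates less well with the follow-up form, that test is less efficient than it need be.

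The choice between TLFB and AUDIT for the primary outcome is a separate matter. The mismatch remains as long as AUDIT is analysed at all, and it is also named as a measure of weekly consumption.

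**Working it through.** **1. The windows side by side**

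| Measure | Baseline | 3 months | 6 months |
|---|---|---|---|
| TLFB | 30 days | 30 days | 30 days |
| AUDIT | routine intake form, window not stated | 3 months | 3 months |

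Only AUDIT changes between levels of the time factor.

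**2. The plan's own figure.** Inputs from Statistical analyses and power calculation: effect 0.4 SD, two-sided alpha 5%, 98 per arm. Power is not stated; I assume 80%.

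n per arm = 2 × ((1.960 + 0.842)/0.4)² = 98.1, which matches 98. In reverse, power = Φ(0.4/√(2/98) − 1.96) = Φ(2.80 − 1.96) = 0.80. The same section ties the calculation to heavy drinking days in the past 30 days, which is the TLFB window, so it does not depend on AUDIT.

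**3. Effect of a common shift.** Let the intake form raise every baseline value by c.

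- Within-arm change: (follow-up mean − baseline mean) − c. The artefact stays in full.
- Difference in change between two arms: −c appears in both arms and cancels.

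Numerical check on one simulated data set (98 per arm, all correlations 0.5, both app arms 0.4 SD lower at follow-up), with c = 1 SD: the arm-by-time F was 2.317 before and after, and the control arm's change at 3 months moved from -0.11 to -1.11 SD.

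**4. When the arm contrast loses power.** Let k be the ratio of baseline SD to follow-up SD and r the baseline to follow-up correlation. The documents give neither, so both are assumed. For two arms and one follow-up, in follow-up SD units:

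- change from baseline: SD = √(1 + k² − 2rk)
- baseline as covariate: SD = √(1 − r²), whatever k is
- power = Φ(2.80/SD − 1.96)

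Example, k = 1.25 and r = 0.5: SD = √(1 + 1.5625 − 1.25) = 1.146, and 2.80/1.146 − 1.96 = 0.48, so power is 0.69.

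| r | Change, k = 1 | Change, k = 1.25 | Covariate |
|---|---|---|---|
| 0.3 | 0.66 | 0.55 | 0.84 |
| 0.5 | 0.80 | 0.69 | 0.90 |
| 0.7 | 0.95 | 0.87 | 0.98 |

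If the mismatch lowered r from 0.6 to 0.5 with equal SDs, power for change would fall from 0.88 to 0.80. If it altered neither r nor k, nothing would be lost.

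**5. The planned three-arm, three-time F test.** Simulation, 3,000 runs, 98 per arm, assumed correlation 0.6 between the two follow-ups, both app arms 0.4 SD better, no sphericity correction.

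- Equal SDs, baseline correlation 0.6, 0.5, 0.4, 0.3: power 0.93, 0.87, 0.79, 0.74, with type I error about 5%.
- Baseline correlation 0.5, SD ratio 1, 1.5, 2: power about 87%, 65%, 45%, and type I error about 4.8%, 6.1%, 7.2%.

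These results show the mechanism. They do not estimate what will happen in this trial.

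**The case against.** The trial's question is the effect of adding the devices to usual treatment. That is a comparison between arms, and a shift common to the arms does not bias it. The analysis section announces no within-arm claim of reduction. A 3-month window at follow-up is also sensible, because the visits are 3 months apart and each interval is covered once. Weekly consumption is a rate, which at constant drinking is the same over any window. TLFB measures the same outcomes with a fixed window. Details of AUDIT scoring may sit in an analysis plan that is not shown.

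Most of this stands, and it limits the point. It does not remove it: the article itself fixes both the changed window and a model in which time, including baseline, is a factor, so an AUDIT time effect will be produced and can be misread.

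Two stronger readings are tempting but unsupported.

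- **That the arm-by-time contrast definitely loses power, perhaps severely.** With a baseline SD twice the follow-up SD and r = 0.5, the change-score formula gives Φ(2.80/√3 − 1.96) = 0.37. But the documents state no AUDIT SD, correlation or baseline window, and a shift in mean alone costs nothing.
- **That AUDIT would show 50% to 75% fewer days with unchanged drinking.** This follows from raw counts over an assumed 6 or 12 months at baseline (1 − 3/6 and 1 − 3/12). Nothing says that AUDIT is analysed as a raw count over its window.

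Nor should the whole gain from covariate adjustment be credited to this point. The step from 0.80 to 0.90 at r = 0.5 arises even when the windows match.

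**Conclusion.** The point holds for AUDIT-based measures only. Their main effect of time and their within-arm change from baseline are partly an artefact of the changed reference period. The size and direction of the artefact cannot be derived, because the intake window is not stated; that it differs is an inference from the wording about modification at follow-up.

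The randomised contrast is not biased by a common shift. Loss of power, or type I error above 5% in the uncorrected F test, is possible but conditional on unequal variances or a weaker baseline correlation. The TLFB and PEth analyses and the sample size are untouched. This is a cheap improvement, not a flaw that threatens the main comparison.

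**What to change.** In Statistical analyses and power calculation, add one sentence for AUDIT-based measures: baseline is not a level of the time factor; arms are compared on the 3- and 6-month values, which share the 3-month window, with intake AUDIT as a covariate (ANCOVA, or a mixed model with arm, visit and arm by visit); AUDIT change from baseline is not interpreted. A covariate need not share the outcome's window or scale, so the intake form can be used as it is.

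The cost is that sentence and no new data. The small downside is that AUDIT change from baseline is no longer reported. If that change is wanted, the 3-month version would also have to be given once before randomization and used as the baseline level.

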### Statistical analyses and power calculation

The sample size has been estimated from the primary outcome variable, heavy drinking days during the past 30 days before baseline, at 3 months and at 6 months after baseline. Based on the assumption that the effect size of the intervention will be in the range of 0.4 SD in groupwise comparisons (alpha 5% and two-tailed tests) we need at least 98 individuals in each of the three treatment arms, and given an expected 25% dropout rate this motivates our choice of *N* = 375.

Data will be analyzed according to intention to treat (ITT). A secondary analysis will be per protocol for those participants who have contributed data at baseline and at 3-month follow-up. Primary and secondary outcome measures will be analyzed through ANOVA for repeated measures, with time (baseline, 3 months, and 6 months) as the dependent variable and type of intervention (TAU, or TAU + Glasklart, or TAU+ iBAC) as the independent variable.

A multiple regression analysis will be performed to investigate the extent to which the different predictor variables (consumption level and pattern, severity of dependence) contribute to the variation in the primary and secondary outcome measures.

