**Methods:**

The study is a three-armed RCT with follow-ups 3 and 6 months after randomization. In total, 375 adults (age 18+ years) diagnosed with alcohol use disorder (AUD) will be invited to participate in a 3-month intervention. The primary outcome is the number of days with heavy drinking, defined as four or more standard drinks (12 g alcohol/drink) and measured by the timeline follow back (TLFB) and Alcohol Use Disorder Identification Test (AUDIT) instruments at 3-month and 6-month follow-up. Secondary outcome measures include weekly alcohol consumption, measured by the TLFB, AUDIT, and phosphatidylethanol in blood values at 3-month and 6-month follow-up (number of days with blood alcohol concentration levels exceeding 60 mg/100 ml).

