#### Randomization

Following the first treatment session, the counselor informs the study coordinator about the new study participant (see Fig 2 for participation flow diagram). The coordinator records baseline data in a study database and initiates the randomization procedure. This procedure is conducted by an administrator with no other role in this study. Randomization is done by a computer program, where participants are randomized (in blocks of 10) either to treatment as usual (TAU), or TAU + Glasklart, or TAU + iBAC. TAU in this study at Riddargatan 1 involves pharmacotherapy in combination with manualized psychological treatment—either the “Guide to better drinking habits”, building on theories on guided self-change [23–25], or the “Guide to Controlled drinking”, referring to theories on behavioral self-control training [26]. Each study participant is given a study number (1–375). Only the administrator has access to the code key, where the study number is coupled with the participant’s person number. The code key is stored in a locked cabinet in the patient archive at the clinic.

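### N = 375 with 25% dropout leaves about 94 participants per arm, not the 98 that the protocol says it needs

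*Protocol article*

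**What the plan says.** The section on statistical analyses and power calculation in the protocol article assumes that "the effect size of the intervention will be in the range of 0.4 SD in groupwise comparisons", with "alpha 5% and two-tailed tests". From this it concludes that "we need at least 98 individuals in each of the three treatment arms, and given an expected 25% dropout rate this motivates our choice"; the total so chosen is 375. It gives neither the power nor the inflation step.

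Two other places show that 375 is the number before dropout. The Methods part of the abstract says "In total, 375 adults (age 18+ years) diagnosed with alcohol use disorder (AUD) will be invited to participate in a 3-month intervention". The Randomization section says "Each study participant is given a study number", and gives the range of these numbers as 1 to 375.

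**The concern.** A sample-size sentence of this form makes a claim that can be checked: after the expected losses, the enrolled number should still supply the required number. Here it does not. The required 98 per arm, the 25% dropout and the total of 375 stand in one sentence, and the third does not follow from the first two.

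At stake is the accuracy of the justification for N. If dropout runs as planned, the trial ends below the minimum it set itself, and the published rationale credits the design with slightly more than it has. The article names sample size among the main criticisms of earlier work in this field, so readers are likely to check this sentence.

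**Working it through.** **Inputs, all from the sample-size paragraph:** standardised difference d = 0.4; two-sided alpha 5%; 98 per arm; three arms; 25% dropout; N = 375. The allocation ratio is not stated. Equal allocation (375 / 3 = 125 per arm) is assumed for the per-arm figures.

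**Step 1. Reproduce the 98.** The power is not given, so 80% is assumed:

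n per arm = 2 × (1.960 + 0.842)² / 0.4² = 98.1

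The stated 98 is this value rounded to the nearest whole number. Strict rounding up gives 99, and the t-test gives 99.1. So the 98 is the usual number before dropout, at an inferred power of 80%.

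**Step 2. Apply the dropout to 375.**

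- Retained in total: 375 × 0.75 = 281.25
- Required in total: 3 × 98 = 294
- Shortfall: 294 − 281.25 = 12.75, about 13 in total
- Per arm: 281.25 / 3 = 93.75 against 98, about 4 short

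The total shortfall depends neither on the unstated power nor on the allocation ratio, because 281 people cannot fill three arms of 98 under any split.

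**Step 3. The N that would satisfy the sentence.**

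- On the total: 294 / 0.75 = 392
- By arm, rounded up: 98 / 0.75 = 130.7, so 131 per arm and 3 × 131 = 393
- Difference from 375: 17 to 18 participants (18 / 375 = 4.8%)

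**Step 4. The dropout that 375 can bear.** 1 − 98/125 = 21.6%.

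**Step 5. Size in power terms.** For an unadjusted two-group comparison at d = 0.4 and two-sided 5%:

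| Per arm | Normal approximation | t-test (noncentral t) |
|---|---|---|
| 98 | 80.0% | 79.6% |
| 93.75 | 78.2% | 77.8% |

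The loss is 1.8 percentage points by either method. The difference detectable with 80% power at 93.75 per arm is (1.960 + 0.842) × √(2 / 93.75) = 0.409 SD by the normal approximation and 0.411 SD by the t-test, so about 0.41 SD.

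**The case against.** The mismatch itself cannot be argued away: nothing else in the article repairs it. Four points on the other side limit what may be made of it.

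- **The effect is small.** About 4 retained participants per arm and 1.8 points of power are at issue. The protocol claims only an effect in the region of 0.4 SD, and 0.41 lies within that. The 25% is itself an expectation, and 21.6% would close the gap. This stands, and it settles the severity.
- **The protocol does not promise 80% power.** A reader might infer that dropout pushes the trial below a stated 80% target. The article gives no target, and by the t-test even 98 per arm gives only 79.6%. Only the gap between 98 and 93.75 is documented. The 80% is this review's assumption.
- **The cause is not documented.** A reader might infer that 98 was multiplied by 1.25 instead of divided by 0.75. That gives 122.5, so 123 per arm and 369 in total, and a further rounding up is needed to reach 375. Starting from 100 per arm gives exactly 125, but the article does not mention 100. The point therefore rests on the mismatch alone.
- **The planned analysis is not a t-test on completers.** The article plans an intention-to-treat repeated-measures ANOVA over baseline, 3 and 6 months, and does not say which visit the 25% refers to. The loss under that model is not established. This stands as a limit on the power figures. It does not rescue the sentence, which bases N on pairwise comparisons with an explicit dropout allowance and takes no credit for partial data or baseline correlation.

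It is also tempting to say that baseline adjustment makes up the loss. The article gives no correlation between baseline and follow-up. With an assumed r and 93.75 per arm, power would be 79.4% at r = 0.2, 81.5% at 0.3, 84.4% at 0.4 and 88.2% at 0.5. Recovery is possible, but cannot be claimed from the document.

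**Conclusion.** The point holds as a small arithmetic error in a stated figure. N = 375 at 25% dropout leaves 281 participants, about 94 per arm, and not the 294 (98 per arm) that the same sentence requires. That much needs no assumption beyond the protocol's own numbers.

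The consequence, about 78% power for 0.4 SD or 80% power for about 0.41 SD, rests on three assumptions: equal allocation, an unadjusted two-group comparison of those retained, and an 80% target inferred from the 98. The documents do not support reading this as a materially underpowered trial or as a reason that enrolment must rise.

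**What to change.** Keep N = 375 and restate the sentence, for example: *125 per arm with 25% dropout leaves about 94 per arm, giving about 78% power for 0.4 SD (80% for about 0.41 SD) in an unadjusted pairwise comparison; 98 per arm is reached only if dropout is at most 21.6%.* State the power target explicitly.

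If the sponsor wishes to mention baseline adjustment, it should appear only as an assumption with its range, from about 79% power at r = 0.2 to about 88% at r = 0.5.

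The cost is one corrected sentence and a slightly less favourable stated power. Design, analysis and enrolment stay as they are. Raising N to 392 or 393 would also make the sentence true, at the cost of 17 or 18 more participants, but the size of the error does not require it.

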**Fig. 2 Fig2:**
[figure not shown]
Participant flow diagram. AUD alcohol use disorder, AUDIT Alcohol Use Disorder Identification Test, ICD 10 International Statistical Classification of Diseases and Related Health Problems 10th revision, ITT intention to treat, TAU treatment as usual, TLFB timeline follow back

At the second treatment session, the counselor collects the signed informed consent document. The counselors then explain and demonstrate the two devices: Glasklart and iBAC. Each patient randomized to the iBAC intervention is provided with an iBAC breathalyzer (one of the smallest breathalyzers available) for the duration of the study. The apps (Glasklart and iBAC respectively) will be installed on the participants’ smartphones. The iBAC breathalyzer is linked to the mobile phone via Bluetooth and the information on the BAC level is saved in the breathalyzer and mobile app. The user identifies herself or himself using a color-coding photographic function to verify that the intended user takes the test.

Patients randomized to Glasklart will be instructed to register every glass of alcohol they drink in the Glasklart app. They will receive automatic reminders, a so-called push notification that pops up on the mobile device after half an hour (after first registration), to continue registration if they have consumed more alcohol (i.e., “do you have anything more to register?”). Patients randomized to iBAC treatment will also receive a message on their mobile phone instructing them to use their iBAC breathalyzer at hourly intervals during drinking occasions, as long as these go on. That is, the iBAC is programmed to contact the patient with push notification according to a preset time schedule. The patients can then review their drinking through the apps respectively. Glasklart will describe the number of drinks consumed, when and where, in what mood, and whether alone or together with others. iBAC will describe the BAC level at different time points. Both of these devices can be viewed on a daily, weekly, or monthly basis. Moreover, the information collected is also visible for the counselors.

At all sessions of the treatment program, at baseline, at 3 months, and at a follow-up after 6 months, the timeline follow back (TLFB) and AUDIT will be recorded, and blood tests will be analyzed for phosphatidylethanol in blood (PEth).

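### TLFB and PEth recorded at every treatment session have no role in the effect analysis, so participants lost before month 3 contribute no post-randomisation drinking data

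*Protocol article*

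**What the plan says.** All places are in the protocol article.

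- **Collection.** The text under Randomization that follows the flow diagram lists when TLFB, AUDIT and PEth are taken: "At all sessions of the treatment program, at baseline, at 3 months, and at a follow-up after 6 months". The Blinding section also foresees assessments while treatment is under way.
- **Analysis.** Statistical analyses and power calculation states: "Primary and secondary outcome measures will be analyzed through ANOVA for repeated measures, with time (baseline, 3 months, and 6 months". The same section sizes the trial on "heavy drinking days during the past 30 days before baseline, at 3 months and at 6 months after baseline". Session measurements are given no role in the effect analysis.
- **Windows.** Under Instruments, the TLFB is a "structured interview for assessment of alcohol consumption during the last 30 days", and AUDIT is "modified to the 3-month reference period in the follow-up". The primary outcome, heavy drinking days, is "measured by the timeline follow back instrument (TLFB) and AUDIT".
- **Duration and dropout.** According to the Abstract, participants "will be invited to participate in a 3-month intervention". The statistical section expects 25% dropout and declares intention to treat.

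**The concern.** The second research question asks whether using the devices changes consumption. The proposed mechanism, self-monitoring, acts while a device is in use. The main count of heavy drinking days is nevertheless compared between arms for only about the last month of that use, and session PEth is not compared at all.

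The more consequential side is dropout. Someone who attends several sessions and leaves before month 3 has drinking data and PEth recorded after randomisation. In an analysis restricted to baseline, 3 and 6 months, that person supplies a baseline value at most, and a classical repeated-measures ANOVA would discard the record altogether. Drinking during treatment is likely to predict the missing 3-month value better than baseline does. Leaving it out makes the missing-data assumption rest on baseline alone, in a trial that expects to lose a quarter of its participants.

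**Working it through.** **1. The plan's own figure.** Inputs from the statistical section: effect 0.4 SD, two-sided 5%, 98 per arm. Power is not stated; 80% is assumed. Then n = 2 × (1.960 + 0.842)² / 0.4² ≈ 98.1 per arm. The t-test solution is 99.1, and power with 98 per arm is 0.80. The 98 therefore reproduces to within rounding.

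**2. Share of the intervention outside the TLFB window.** With D days of intervention the share is (D − 30)/D. For 90 days it is 60/90 = 66.7%; for 92 days it is 62/92 = 67.4%. The 6-month window lies after the intervention.

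**3. Numbers at stake.** 375/3 = 125 per arm. With 25% dropout, 31.25 are lost and 93.75 remain. The article does not split dropout by visit, so 31.25 is an upper limit for losses before month 3.

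**4. Information at month 3.** As an approximation, effective n = 93.75 + 31.25 × R², where R² is the share of variance in the missing 3-month value explained by the data used. None of the inputs below is in the documents.

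| Data used for dropouts | Assumption | Effective n per arm |
|---|---|---|
| Baseline only | correlation 0.3, R² = 0.09 | 93.75 + 2.81 = 96.6 |
| Baseline only | correlation 0.4, R² = 0.16 | 93.75 + 5.00 = 98.8 |
| Baseline and last session, sessions for 50% | R² = 0.37, otherwise 0.09; mean 0.23 | 93.75 + 7.19 = 100.9 |
| Baseline and last session, sessions for 100% | R² = 0.50 | 93.75 + 15.63 = 109.4 |

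The R² values of 0.37 and 0.50 correspond to correlations of 0.6 and 0.7 between last session and month 3, with baseline-to-session correlations of about 0.35 and 0.45.

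**5. Check on the approximation.** The large-sample formula for a mean under monotone missingness is 1/n_eff = (1 − R²_bs)/n_c + (R²_bs − R²_b)/n_s + R²_b/n. Here n_c = 93.75 completers, n_s = those with session data, n = 125, and b and bs denote baseline and baseline plus session.

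- Baseline only: 95.9 to 97.7.
- R²_bs = 0.37, R²_b = 0.09, n_s = 109.375: 1/(0.00672 + 0.00256 + 0.00072) = 100.0.
- R²_bs = 0.50, n_s = 125: 1/(0.00533 + 0.00400) = 107.1.

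The simple rule is thus one or two participants optimistic; the size of the gain is unchanged.

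**The case against.** **The endpoint is a legitimate choice.** Outcomes are placed consistently at 3 and 6 months, and a 30-day window at the end of treatment is a sound target. This stands. The documents do not contradict themselves here, and the main outcome need not change.

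**AUDIT reaches back over the whole intervention.** This also stands. A reader might infer that the first 60 days enter no comparison at all. That is too strong, because AUDIT is co-named for the primary outcome and has a 3-month reference period at follow-up. But it gives a frequency category, not a count of heavy drinking days, and it too is missing at month 3 for anyone lost earlier.

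**Not all dropouts are affected.** A reader might infer that in-treatment data on every dropout are wasted. Those lost after month 3 still supply their 3-month value, and the article names those with baseline and 3-month data as its per-protocol set.

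**Power could be said to suffer badly.** A reader might argue that an effect fading by month 3 would be missed. With 94 per arm and correlations of 0.5–0.8 between 30-day periods, effects of 0.4, 0.4 and 0.2 SD give 28% power at month 3 against 69–80% for the three-period mean. But effects of 0, 0.2 and 0.4 SD reverse this: 78% at month 3 against 31–39% for the mean. The documents favour neither pattern, so these figures cannot support the point.

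**Session data are awkward.** Randomisation follows the first session and devices are demonstrated at the second, so a 30-day recall at an early session mostly covers days before randomisation or device use. The number and spacing of sessions are not given. Attendance is post-randomisation behaviour that may differ by arm, and follow-up visits are held by the study coordinator, so assessment conditions may differ. All of this stands and limits the gain.

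**An unseen SAP may settle it.** It may supply missing-data handling, and silence on that is not held against the article. But the article itself names the model and its time levels, and a SAP that used session data would need to be reconciled with that statement.

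**Conclusion.** The point holds as a limited one. The named analysis leaves out repeated post-randomisation measurements of its own outcomes that the trial already plans to collect. About 67% of the intervention lies outside the 3-month TLFB window, and participants lost before month 3 contribute nothing after randomisation. This is lost information and weaker protection against dropout bias, not an error in the endpoint.

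The precision gain is modest: from about 97–99 to about 101–109 effective participants per arm at month 3. It rests on assumed correlations with the 3-month value (0.3–0.4 for baseline, 0.6–0.7 for the last session), on session data existing for 50–100% of dropouts, and on all dropout falling before month 3. If useful session data are scarce among early dropouts, the gain shrinks towards zero. The stronger reason for the change is that the missing-at-random assumption could then condition on drinking during treatment as well as at baseline.

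**What to change.** - Keep heavy drinking days in the 30 days before the 3-month visit as the main outcome.
- Replace the three-level ANOVA with a likelihood-based repeated-measures model. Add session TLFB as earlier post-randomisation time levels, for example days 1–30 and 31–60, counting only days after randomisation and treating uncovered days as missing. Use post-randomisation session PEth in the same way for the PEth outcome.
- Report the device-versus-TAU difference over days 1–90 as a pre-specified secondary contrast only.
- State the number and expected spacing of sessions, report session attendance by arm, and add a sensitivity analysis without session data. The last two show whether differing attendance or assessment conditions drive the result.

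The cost is analysis wording and some data entry, with no new visit, interview or blood sample. The remaining downsides are partial coverage of the early periods, session timing that may carry information about drinking, and early recalls that add little once days before randomisation are removed.
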